## Methods

### Overview

We will conduct a prospective longitudinal cohort study. Participants will be recruited online. We will apply best cohort study recruitment practices using meditation teachers and center networks [47]. After providing informed consent, participants will be requested to complete a series of self-report measures via online surveys hosted on the Qualtrics (Qualtrics International Inc) survey platform [48] and delivered through the ambulatory assessment mobile phone app Fabla (Emory University) [49], which will additionally support the collection of voice recordings within the app. This capability will be leveraged for participant verification, as described below, and for future qualitative analysis of the impact of meditation practice. There will be assessment time points at baseline and one year, and at weekly and monthly intervals in between, as shown in Table 2. For each survey, participants will receive mobile phone push notifications and email reminders. Example in-app images of the participant experience of data collection are displayed in Multimedia Appendix 1.

**Table 2. T2:** Timeline from participant commencing the study.

Time	Start	Day 1	Day 2	Day 3	Day 4	Day 5‐11	Day 34	After 2 months of no practice reports	12 months
Action	Expression of interest survey	Consistent response check survey	Baseline survey	Fabla (Emory University) download survey	Fabla induction measures	Commence weekly measures	Commence monthly measures	Triggered follow-up survey	Outcome measurement
Access method	Advertising or website links	Email	Email	Email	Fabla	Fabla	Fabla	Email	Email

### Ethical Considerations

This study was approved by the Science, Technology, Engineering, Mathematics, and Medicine (STEMM 3)–Greater Than Low Risk (GTLR) human research ethics committee at the University of Melbourne on August 12, 2024 (reference: 2024-30046-56865-3). All participants will provide informed consent. Participants will be compensated at US $16 per hour rate for each baseline, monthly, and yearly survey completed and via entries in a gift card draw for each approximately 2-minute weekly survey.

### Participant Selection Criteria

We will recruit beginner meditators who have completed initial instruction in MBPs and 2 Buddhist traditions that have informed MBPs, Theravada, and Mahayana [50]. While all these traditions emphasize a focus on observing experiences and one’s responses to experiences, spiritual traditions often interpret these processes via specific lenses (eg, the Four Noble Truths in Theravada) and soteriologies that affect implicit and explicit motivations for a practice [51]. In addition, each tradition has exclusive introspective and reflective tools (eg, koans in Zen within Mahayana) that may be applied within meditation practices or in other aspects of life. Furthermore, the practice, social, and community contexts vary widely (eg, spaces, teachers, rituals, and other activities). The inclusion of these traditions will facilitate rich insights into the effects of diverse settings while keeping a meaningful focus.

Participants will be included if they are adults aged 18 years or older; reside in Australia, New Zealand, the United Kingdom, or the United States; have completed an initial introductory meditation course, initial instruction, or regular practice (at least 40 minutes per week) for at least a month in one of the eligible traditions (Buddhist Mahayana or Theravada or mindfulness meditation, including MBPs and apps that incorporate mindfulness meditation) in the last 4 months; and if they intend to continue practicing meditation regularly in the eligible meditation tradition. We are recruiting participants with some meditation experience rather than those with no lifetime practice hours to examine a naturalistic sample of people who independently seek out and continue meditation practice. This sample will also support the study retaining participants who continue practicing meditation for one year, and therefore have sufficient power in our primary analysis, as significant dropout is common in the first weeks of meditation practice [52-55].

Participants will be excluded if they have less than one month of experience in their meditation practice (with the option to defer enrollment until they satisfy this criteria), if they have regular meditation experience (meditating at least 40 minutes per week) for one month or more in any tradition prior to the last 4 months, or if they are monastics or have a similar formal role in a religious community and/or they reside in a religiously affiliated dwelling (eg, monastery).

### Participant Verification

The study uses a combination of methods to both discourage nongenuine participants and to verify that those participants who are recruited are genuine. Entry into the study involves 4 Qualtrics surveys delivered on consecutive days, followed by download of the app Fabla, which is restricted to Australia, New Zealand, the United Kingdom, or the United States, before commencing the weekly survey schedule, as shown in Table 3. The first expression of interest survey will exclude participants who fail Qualtrics internal bot checks and who are detected to be outside our recruitment countries. The second survey will repeat date of birth questions from the expression of interest to detect inconsistent responses.

**Table 3. T3:** Schedule of measures.

Measures	Baseline	Weekly	Monthly	1 year
Outcome measures				
Health and well-being (EQ-HWB-S^a^)	✓		✓	✓
Mental well-being (SWEMWBS^b^)	✓		✓	✓
Independent variables				
Meditation practice frequency and duration		✓		
Meditation practice characteristics	✓		✓	✓
Secular or spiritual practice tradition	✓		✓	✓
Covariates				
Meditation history	✓			
Sociodemographics	✓			
Physical and mental health status	✓			✓
Other variables				
Cost of meditation practice	✓		✓	✓
Cost of mental health care use	✓		✓	✓
Meditation-related adverse effects scale (MRAES)	✓		✓	✓

a EQ-HWB-S: EQ Health and Wellbeing—Short version.

b SWEMWBS: Short Warwick-Edinburgh Mental Well-Being Scale.

After we have received 7 separate survey responses from participants, their IP and internet service provider (ISP) will be inspected. This IP inspection identifies participants whose IP addresses change on each survey, which indicates possible “residential proxy” use, those who have IP addresses associated with a known virtual private network (VPN), those who have more than 2 ISPs associated with their IPs, and those who have IP addresses associated with a data center (eg, Amazon Web Services).

Participants who are identified by these IP inspections will be manually screened by listening to voice recordings they will provide in Fabla. Those participants who we are not able to verify through this process will be contacted and offered an online interview. Prospective participants who do not respond after follow-up, refuse an interview or alternative contact method, or are suspected to be nongenuine during an interview will be considered nongenuine, excluded from further participation, and have their data removed.

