**Methods:**

We will conduct a prospective longitudinal cohort study of 600 beginner meditators in Australia, New Zealand, the United States, and the United Kingdom over a 1-year period. Meditation practice frequency and duration will be reported weekly through the ambulatory assessment app Fabla (Emory University), with sampling of the primary outcome of quality of life and secondary outcome of mental well-being at monthly intervals. Practice characteristics, including secular versus spiritual practice, will also be reported monthly, as will the costs of meditation and mental health care and the incidence, severity, and duration of any adverse effects. Potential confounders, including baseline mental health symptoms, social support, and sociodemographics, will be controlled for in linear mixed models. An incremental cost-effectiveness ratio will be calculated, and sensitivity analyses will be conducted.

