Finally, the study aims to document the incidence and impact on daily function of any challenging, difficult, or distressing meditation-related experiences (Aim 6). Meditation-related adverse effects (MRAEs) will be defined as any challenging, difficult, or distressing meditation-related experiences that impact everyday functioning. Our aims, hypotheses, and possible interpretations are summarized in Table 1 below.

**Table 1. T1:** Protocol Design table.

Question	Hypothesis	Sampling plan (eg, power analysis)	Analysis plan	Interpretation given to different outcomes
Does regular meditation practice after initial instruction increase quality of life?	The amount of meditation practice during approximately the first year predicts practitioners’ quality of life, such that a greater amount leads to greater quality of life.	A total number of 522 gives 95% power to detect the variance in quality of life (EQ-HWB-9^a^) explained by monthly meditation practice observed in linear mixed model analysis, at a 2-tailed significance level of 0.05, accounting for an estimated 20% loss to follow-up.	Linear mixed model of the fixed effect of the amount of meditation in the past month on quality of life in the past week (EQ-HWB-9), controlling for the confounding factors of age, caring status, education, mental health diagnosis, commitment to meditation, and membership of a practice support community at baseline.	A positive/negative and statistically significant association between the amount of meditation in the past month on quality of life and in the past week will suggest that regular meditation practice after initial instruction increases/decreases quality of life in a linear fashion. A nonsignificant association will suggest an absence of evidence for either of these effects.

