Community of practice membership will be assessed by a single item and recorded at baseline and one year (“Are you an active member of a community of practice [eg, sangha, meditation group, or online communities]? Yes/No”). This will be a covariate.

Age in years will be recorded at baseline. This will be a covariate.

Caring status, including type of caring relationship, will be assessed at baseline. This will be a covariate.

Education will be assessed by a question asking, “What is the highest level of education you have completed?” and will be recorded at baseline. This will be a covariate.

Mental health diagnosis will be assessed by a single item at baseline (“Have you ever been diagnosed with a mental illness by a clinician?” Yes/No/Prefer not to say). This will be a covariate.

The cost of meditation practice will be assessed through self-reported questions asking participants whether they have spent any money related to their meditation practice, including on classes, courses, retreats, smartphone apps, resources such as mats, books, and clothes, and donations to meditation teachers or centers. These questions will be asked at baseline, monthly, and one year later.

The cost of mental health care use will be assessed via questions on type, frequency, and costs of psychological support. Specifically, participants will be asked, “In the past month, how many times did you see a… psychologist, psychiatrist, social worker, counselor, or other.” Participants will then be asked how they paid for this mental health service use (eg, “Out-of-pocket” and “Publicly funded”) and their out-of-pocket expenditure on mental health services in the past month. These questions will be asked at baseline, monthly, and one year. This will be used in the economic evaluation.

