For hypothesis 1, we will perform linear mixed model analysis of the fixed effect of the amount of meditation in the past month on quality of life in the past week (EQ-HWB-9), controlling for the potentially confounding baseline factors of age, caring status, education, mental health diagnosis, commitment to meditation practice, and membership of a meditation practice community at baseline. This model will allow us to assess how meditation as practiced by our participants under naturalistic conditions contributes to their quality of life, controlling for baseline differences related to time available for practice, symptom severity, motivation, and social support. If we detect an effect of meditation practice, we will perform sensitivity analysis to examine how robust this effect is to time-varying confounders by using inverse probability weighting of meditation in the last month to examine if the association would still be present if practice that month had varied independently of prior practice and benefit.

For hypothesis 2, we will perform linear mixed model analysis of the fixed effect of the amount of meditation in the past month on mental well-being in the past 2 weeks (SWEMWBS), controlling for the potentially confounding factors of age, caring status, education, mental health diagnosis, commitment to meditation practice, and active membership of a meditation practice community at baseline. If we detect an effect of meditation practice, we will again perform time-varying confounding sensitivity analysis with inverse probability weighting.

For hypothesis 3, we will add the variable capturing whether participants practiced secular meditation traditions (with no more than one month of reported practice in a spiritual tradition) versus engaging in spiritual traditions and its interaction term with the amount of meditation to the model for hypothesis 1. This initial analysis will allow us to assess whether predominantly secular meditation has a differential effect from meditation that incorporates spiritual practices, as practiced in real-life contexts, while retaining sufficient power. If we detect an effect, we will perform further exploratory analysis into what may be driving this difference. We will also describe the groups in terms of meditation practice characteristics, including proportion of practice types and social context.

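### The article says baseline symptoms and symptom severity are controlled, but the only health term in the H1–H4 models is a lifetime-diagnosis item, and physical health and meditation history, covariates in Table 3, are in no model

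*Protocol article*

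**What the plan says.** Three places in the protocol article describe what is adjusted for, and a fourth defines the variable used.

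- Abstract, Methods: "Potential confounders, including baseline mental health symptoms, social support, and sociodemographics, will be controlled for in linear mixed models".
- Table 3 (Schedule of measures): under Covariates, the rows "Meditation history" and "Physical and mental health status" are both ticked at baseline, alongside sociodemographics.
- Analysis Plan, hypothesis 1: the covariates are "age, caring status, education, mental health diagnosis, commitment to meditation practice, and membership of a meditation practice community at baseline". The next sentence describes this model as "controlling for baseline differences related to time available for practice, symptom severity, motivation, and social support". Hypothesis 2 has the same six covariates, Table 1 repeats them for all four hypotheses, and hypotheses 3 and 4 add only the secular/spiritual variable and its interaction with practice amount.
- Measures: mental health diagnosis is one baseline item, "Have you ever been diagnosed with a mental illness by a clinician", answered yes, no or prefer not to say.

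**The concern.** An ever-diagnosed item does not measure current severity. A person who recovered years ago and a person who is acutely unwell give the same answer, and an undiagnosed person with marked symptoms answers no. The model therefore does not control what the Abstract and the Analysis Plan say it controls. Physical health has no term at all, although the Measures section says the primary outcome includes physical aspects such as pain.

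This matters because participants choose how much they meditate, and Table 1 interprets a significant coefficient as practice increasing or decreasing quality of life. Baseline health can plausibly affect both practice and score. The direction is not known in advance. If healthier people practise more, a benefit is exaggerated; if people in difficulty practise more, a real benefit can be hidden. The Discussion expects modest effects, where such bias weighs most. Its limitations paragraph mentions expectancy and placebo but not confounding by health.

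**Working it through.** No stated figure has to be reproduced. The check is a comparison of the covariate lists.

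| Item | Abstract, Methods | Table 3, Covariates | Models (Table 1, Analysis Plan) |
|---|---|---|---|
| Mental health symptoms or severity | Said to be controlled; severity claimed again in the Analysis Plan | Mental health status row | Lifetime diagnosis only |
| Physical health | Not named | Listed | No term |
| Meditation history | Not named | Listed | No term |
| Sociodemographics | Said to be controlled | Listed | Age, caring status, education |
| Social support | Said to be controlled | No row of that name | Community membership |

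The last two rows can be matched to model terms. The first is matched only by a poor proxy, and the second and third by nothing.

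**Illustration of size.** Let U be current severity, D the diagnosis item, a = corr(dose, U), ρ = corr(D, U), and b the standardised effect of U on EQ-HWB-9. If D is independent of dose given U, in a standardised linear model:

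- share of confounding left after adjusting for D = (1 − ρ²)/(1 − a²ρ²);
- bias in points per SD of dose = a × b × share × 7.0, where 7.0 is the EQ-HWB-9 SD in the Sampling Plan.

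None of a, b or ρ is in the documents. The assumed ranges are a 0.1 to 0.3, b 0.5 to 0.7 and ρ 0.3 to 0.7.

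- Low end (a 0.1, b 0.5, ρ 0.7): share = 0.51/0.9951 = 0.513; bias = 0.1 × 0.5 × 0.513 × 7.0 = 0.18 points.
- Middle (a 0.2, b 0.5, ρ 0.5): share = 0.75/0.99 = 0.758; bias = 0.2 × 0.5 × 0.758 × 7.0 = 0.53 points.
- High end (a 0.3, b 0.7, ρ 0.3): share = 0.91/0.9919 = 0.917; bias = 0.3 × 0.7 × 0.917 × 7.0 = 1.35 points.

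For scale, the Sampling Plan assumes final gains of 0, 2.25 and 4.5 points for low, medium and high practice, or 2.25 per level. With three equal groups (an assumption) the SD of level is √(2/3) = 0.816, so the planned effect is 2.25 × 0.816 = 1.84 points per SD of dose at the last time point. Averaged over a steady rise it is about half that: 1.125 × 0.816 = 0.92. The ratio of bias to planned effect then runs from 0.18/1.84 = 10% to 1.35/0.92 = 147%. A range that wide shows that the assumptions drive the result. It does not estimate the bias in this study. It also ignores whatever the other five covariates absorb.

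**The case against.** The strongest defence is that the adjustment set is consistent wherever a model is written out. The Measures section flags the same six baseline items as covariates that appear in Table 1 and the Analysis Plan. Table 3 is a schedule, and its rows may be category labels: sociodemographics for age, caring status and education, and health status for the diagnosis item. This stands in part. It does not account for the word physical or for meditation history, and it does not rescue the explicit claims about symptoms and severity.

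A second defence is mitigation elsewhere. The Analysis Plan has inverse probability weighting directed at prior practice and benefit, and its missing-data text mentions a longitudinal constrained analysis that might handle the baseline outcome. But the weighting is a sensitivity analysis run only if an effect is detected, so a benefit masked by confounding would never trigger it. The constrained analysis is named only for missing data, the baseline outcome is in no covariate list, and Table 3 schedules practice amount weekly with no baseline value. How a baseline row would enter a model of past-month practice is therefore unstated.

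Several stronger readings are tempting but unsupported:

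- A reader might infer that the Abstract and Table 3 both promise control of symptoms, physical health and meditation history. They do not. The Abstract names symptoms only; Table 3 names health status and history, and labels them covariates without describing an adjustment.
- A reader might infer that country of residence was also promised. It is nowhere named as a confounder.
- A reader might treat meditation history as an equally serious gap. The eligibility criteria exclude anyone with a month or more of regular practice before the last four months, so its range is narrow.
- A reader might assume that suitable health data are certainly in hand. The article describes no symptom scale, physical-health instrument or history measure, and a condensed article may leave that detail to the full protocol.

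**Conclusion.** The contradiction holds and rests on the printed text alone. The article claims control of baseline symptoms and symptom severity, yet its models contain only a lifetime-diagnosis item for health. Table 3 also lists physical health and meditation history as covariates, and no model uses them. With self-selected practice and a causal reading in Table 1, this leaves avoidable confounding by baseline health in the primary analysis.

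Its size and direction cannot be derived from the documents. The half-to-nine-tenths residual share, and any percentage of the planned effect, follow from assumed correlations and should not be quoted as findings. Symptom severity and physical health are the main omissions; meditation history is minor. The point should be corrected before analysis, but it does not invalidate the design.

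**What to change.** Add to the models for hypotheses 1 to 4 the baseline physical and mental health status measures scheduled in Table 3, and the baseline value of the outcome: EQ-HWB-9 for hypotheses 1 and 3, SWEMWBS for 2 and 4. If the constrained analysis is meant to treat the baseline score as a response, say so and do not also enter it as a covariate. Meditation history can be added as a lesser covariate. Then make the Abstract, Table 1, Table 3 and the Analysis Plan list the same covariates.

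If the baseline survey holds no usable symptom or health measure, one cannot be obtained at baseline for the 341 participants who had already completed it by May 14, 2026. In that case remove the statements that symptoms and symptom severity are controlled, relabel the Table 3 rows, and state residual confounding by health as a limitation. The baseline outcome can still be used, since both scales are scheduled at baseline.

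The cost is a change of wording and a few degrees of freedom in about 600 participants. No new data collection is needed if the Table 3 measures are usable.

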### Measures

A schedule of measures is shown in Table 3 and described in detail below.

Meditation practice frequency and duration will be assessed weekly. Participants will be asked how many days they practiced in the past week, the average number of sessions per day, and the average minutes per session. This is a weekly modification of the timeline followback method, which is the gold standard for reporting in substance use literature, and has been validated for exercise reporting [32] and online administration [56]. We have also validated this question format against a log of meditation timer practice data [32]. Weekly measurement supports accurate reporting in similar methods [57], while allowing us to calculate the amount of meditation each month. This will be our independent variable.

Meditation practice characteristics, including type (eg, meditation with movement such as walking meditation or mindful observation such as observing thoughts or emotions), guided versus unguided sessions (eg, “I work with a teacher or instructor” or “My practice is self-guided”), and social context of their practice (eg, “I practice in a group” or “I practice alone”), will be recorded monthly. These measures will be used to describe the sample by reporting the frequency of each practice type and context reported by participants over one year.

Secular or spiritual meditation practice will be assessed at baseline and monthly by a single item (“In the past month, what meditation traditions have you practiced in?”). Participants will be divided into 2 groups at follow-up; those who both nominated secular meditation as their tradition at baseline and reported a maximum of one month of practice in any spiritual tradition over the follow-up period, versus all participants who practiced in spiritual traditions for 2 months or more during the year. This division will facilitate investigating if those meditation practitioners who practice in spiritual traditions experience the same effects as secular practitioners, while allowing for some dabbling in different traditions by participants. This will be a covariate.

Commitment to meditation practice will be assessed at baseline with a single item (“How committed are you to practicing meditation?” Rate 1‐10). This will be a covariate.

Community of practice membership will be assessed by a single item and recorded at baseline and one year (“Are you an active member of a community of practice [eg, sangha, meditation group, or online communities]? Yes/No”). This will be a covariate.

Age in years will be recorded at baseline. This will be a covariate.

Caring status, including type of caring relationship, will be assessed at baseline. This will be a covariate.

Education will be assessed by a question asking, “What is the highest level of education you have completed?” and will be recorded at baseline. This will be a covariate.

Mental health diagnosis will be assessed by a single item at baseline (“Have you ever been diagnosed with a mental illness by a clinician?” Yes/No/Prefer not to say). This will be a covariate.

The cost of meditation practice will be assessed through self-reported questions asking participants whether they have spent any money related to their meditation practice, including on classes, courses, retreats, smartphone apps, resources such as mats, books, and clothes, and donations to meditation teachers or centers. These questions will be asked at baseline, monthly, and one year later.

The cost of mental health care use will be assessed via questions on type, frequency, and costs of psychological support. Specifically, participants will be asked, “In the past month, how many times did you see a… psychologist, psychiatrist, social worker, counselor, or other.” Participants will then be asked how they paid for this mental health service use (eg, “Out-of-pocket” and “Publicly funded”) and their out-of-pocket expenditure on mental health services in the past month. These questions will be asked at baseline, monthly, and one year. This will be used in the economic evaluation.

Quality of life will be assessed at baseline, monthly, and one year, using the 9-item EQ Health and Wellbeing (EQ-HWB-9) instrument [58]. The EQ-HWB-9 captures mental (eg, depression and cognition), physical (eg, pain), and social (eg, loneliness) aspects of quality of life for the past 7 days, on a 5-point Likert scale from 1 (No difficulty) to 5 (Unable). Previous responsiveness to change analysis indicates that the EQ-HWB-9 detects meaningful changes in both mental and physical health measures [59]. This will be our primary outcome. The EQ-HWB-9 also allows for the calculation of quality-adjusted life years (QALYs), a standard measurement in health decision-making, and thus allows for the comparison of both effectiveness and cost-effectiveness with many other interventions and standard treatments [60].

Mental well-being will be assessed at baseline, monthly, and one year using the Short Warwick-Edinburgh Mental Well-Being Scale (SWEMWBS) [61,62]. The SWEMWBS includes 7 items that assess mental well-being over the past 2 weeks, on a 5-point Likert scale from 1 (None of the time) to 5 (All of the time). This will be our secondary outcome. The items in the SWEMWBS are positively worded (eg, “I’ve been feeling optimistic about the future”) and aim to capture variation in the flourishing side of the well-being spectrum, which will supplement detailed variation in the quality of life deficits captured by the EQ-HWB-9. Previous analyses of responsiveness to change indicate that the SWEMWBS detects individually meaningful improvement across a variety of mental health measures [63].

MRAEs will be measured at baseline, one year, and monthly, using the 3-item MRAEs measures [42]. The first item asks participants to indicate the frequency of any challenging, difficult, or distressing meditation-related experiences, with options ranging from “never” to “frequently.” The second item assesses the level of impairment caused by these experiences on the participant’s ability to function, with options ranging from “not at all” to “severely.” The third item asks about the duration of the impairment, with options ranging from “1 day or less” to “1 year or longer.”

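### The 12-month email survey collects both outcomes but not practice amount, so 12-month outcomes from participants who have stopped weekly reporting cannot be used for Hypotheses 1 and 2

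*Protocol article*

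**What the plan says.** **Exposure.** The Measures section states "Meditation practice frequency and duration will be assessed weekly". Participants give days practised, sessions per day and minutes per session. The monthly amount is built from these reports: "Weekly measurement supports accurate reporting in similar methods [57], while allowing us to calculate the amount of meditation each month". This amount is named as the independent variable. In Table 3 the row "Meditation practice frequency and duration" has a single tick, under Weekly.

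**Outcomes.** "Quality of life will be assessed at baseline, monthly, and one year, using the 9-item EQ Health and Wellbeing (EQ-HWB-9) instrument". The secondary outcome follows the same schedule: "Mental well-being will be assessed at baseline, monthly, and one year using the Short Warwick-Edinburgh Mental Well-Being Scale (SWEMWBS". Table 3 ticks both at baseline, monthly and 1 year.

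**Delivery.** Table 2 (Overview) puts the weekly and monthly measures in the Fabla app. The 12-month entry, "Outcome measurement", goes by email. So does a follow-up survey triggered "After 2 months of no practice reports".

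**Model.** The Analysis Plan fits linear mixed models with the past month's practice amount as the fixed effect on EQ-HWB-9 (Hypothesis 1) and SWEMWBS (Hypothesis 2). It uses REML under a missing-at-random assumption stated for outcome data, with inverse probability of censoring weights as a sensitivity analysis. Aim 5 takes participants who did not continue meditating as the comparator.

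**The concern.** The 12-month survey is the one scheduled outcome measurement that does not depend on the app, so it can still reach someone who no longer opens the app. The exposure, however, exists only in the weekly app reports. For that person the survey returns a value for the left-hand side of the model and nothing for the right-hand side.

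Two things are at stake. First, the lost rows plausibly lie disproportionately at the low end of practice, where the cohort may be thin because everyone enrolled intends to continue. Second, Aim 5 needs to know who stopped meditating. Without a practice question at 12 months, stopping the reports and stopping the practice look alike in the data, even where the 12-month outcome and costs are in hand.

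**Working it through.** **1. The schedule, side by side**

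| Item | Where stated | Weekly (app) | Monthly (app) | 1 year (email) |
|---|---|---|---|---|
| EQ-HWB-9 | Measures; Table 3 | no | yes | yes |
| SWEMWBS | Measures; Table 3 | no | yes | yes |
| Practice amount | Measures; Table 3 | yes | no | no |
| Practice characteristics | Measures; Table 3 | no | yes | yes |
| Tradition | Measures; Table 3 | no | yes | yes |

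The practice items ticked at 1 year do not replace the amount. The characteristics item is described as "Meditation practice characteristics, including type (eg, meditation with movement such as walking meditation or mindful observation such as observing thoughts or emotions", plus guidance and social context. The tradition item asks which traditions were practised. Neither gives days, sessions or minutes.

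**2. What the model needs.** A row enters the Hypothesis 1 or 2 model only if it has both an outcome and a past-month amount. For a participant who is no longer reporting weekly, the month-12 row has the outcome only. REML uses the observed outcomes given the predictors; it does not fill in a missing predictor. Censoring weights reweight the rows that are present and do not restore this one.

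**3. The plan's own loss figure.** The Sampling Plan takes 435 participants, allows 20% loss and states 522. This reproduces as 435 × 1.20 = 522.

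**4. Ceiling on affected participants.** Suppose that all of the 20% are app-leavers who nevertheless answer the 12-month email:
- 0.20 × 522 = 104.4, about 104
- 0.20 × 600 = 120 (the cohort size in the Abstract)
- 0.20 × 627 = 125.4, about 125 (the size given for Hypothesis 3)

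The documents give no 12-month response rate for this group. With an assumed rate r, the count for 600 is 120 × r: 0 at r = 0, 40 at one third, 80 at two thirds, 120 at r = 1.

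**5. What is lost and what is kept.** This is a simulated illustration. Its assumptions are not in the documents: 600 participants; each leaves the app with probability 20%, at a month uniform on 0 to 11; everyone else reports throughout; everyone answers at 12 months.
- Leavers: 117. Of these, 110 still enter the model through earlier months; 7, who left before the first monthly report, contribute nothing.
- Month-12 outcomes obtained: 600. Usable: 600 − 117 = 483.
- All rows with an outcome: 6,550. Usable: 6,550 − 117 = 6,433, and 6,433 / 6,550 = 98.2%.

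The loss is therefore small over the whole data set and concentrated at month 12, where 117 / 600 = 19.5% of the outcomes obtained are unusable in this favourable-response scenario.

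**The case against.** **Leavers are not shut out.** A reader might infer that participants who leave the app cannot enter the models at all. The documents do not support that. Outcomes are monthly and the model is a mixed model, so every earlier month with both values counts. This objection stands, and it limits the point to one late row per leaver.

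**Stopping practice is not stopping reports.** The weekly survey asks how many days were practised, so someone who quits can report zero and stay in the data. Weekly surveys earn prize-draw entries, monthly surveys are paid, and the Overview promises email reminders for every survey. This stands too: that the lost rows are mostly low-practice is plausible but not shown.

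**The 20% is loss to follow-up.** Someone who answers at 12 months is not plainly lost, so the 20% gives a rough ceiling and not an estimate. Accepted.

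**The triggered survey may cover this.** A reader might infer that it carries no measures, since Table 3 has no column for it. The article condenses a fuller protocol, and the survey's content may be set there; it may well ask about practice. Its trigger can also be read as two months of reporting no practice. No finding is made on it.

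**Attrition is already addressed.** Censoring weights do target selective dropout, and the 12-month survey also serves Aims 5 and 6. Both are true, but neither gives the month-12 row an exposure value.

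**The tradition item at 1 year** refers to the past month and might show whether any practice took place. Its response options are not given, and it cannot give an amount.

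**Weekly reports were chosen for accuracy.** The article criticises an earlier study for a rough estimate of practice. That is a reason to keep recall secondary and flagged. It is weaker for rows that otherwise have no exposure value.

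**Conclusion.** The point holds in a limited form. As scheduled in Tables 2 and 3, a 12-month outcome from a participant who has stopped weekly reporting has no past-month amount, so it cannot be used for Hypothesis 1 or 2. The same person cannot be reliably placed in either Aim 5 group.

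The size is at most one row per such participant. The ceiling is about 120 of 600, reached only if the whole assumed 20% loss consists of app-leavers who answer at 12 months; the true number is unknown and could be small. In the illustration, over 98% of outcome rows remain usable. This does not invalidate the primary analysis. It is a gap in a stated schedule that can be closed cheaply.

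**What to change.** In Table 3, tick practice frequency and duration at 1 year, and add the three existing questions (days, sessions, minutes), worded for the past month, to the 12-month email survey.

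Keep the weekly reports as the primary source. Use the recalled amount only where that month's weekly reports are absent, flag those rows, and report Hypotheses 1 and 2 with and without them. Use the same answers to help class participants as continuing or not for Aim 5.

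The cost is three questions in one survey and a minor amendment. The downside is that past-month recall is less accurate than weekly reports and would be used only for non-reporters, so its error would differ by dropout status; the with/without comparison is there to show whether that matters.

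The timing is favourable. Data collection began on October 28, 2025, so no participant had reached 12 months at the May 14, 2026 status date.
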